## Background

Harmful alcohol use begins in adolescence, a period characterized by developments in cognition, behavior and brain maturation. Onset of alcohol use by 14 relative to 21 years of age strongly predicts elevated risk for severe alcohol use problems, with 27% versus 4% of individuals exhibiting alcohol dependence within 10 years of onset [1]. The reasons for this increased vulnerability to alcohol effects in youth need to be clarified.

Important maturational changes in brain anatomy, connectivity, and function continue well into late adolescence. Longitudinal empirical evidence suggests that brain maturation in both grey and white matter follows a postero-anterior trajectory across the cortex [2–4], where frontal areas, and white matter tracts that originate there, mature in parallel with higher order executive functional changes in later adolescence (e.g., inhibitory performance [5] or working memory [6]), relative to other, more basic cognitive functions (e.g., attention). On a functional basis, there is preliminary evidence for the dual system model [7, 8], in which top-down cognitive control networks develop linearly with age between childhood and adulthood [9, 10], while the reward sensitivity system (striatum, medial and orbital prefrontal cortices) follows a non-linear maturation that eventually caps by mid-adolescence [11].

When looking at the effects of alcohol misuse on brain maturation, neuropsychological studies in youth suggest that early alcohol abuse correlates with cognitive impairments in verbal, non-verbal and spatial working memory tasks, as well as attention and executive functions [12–14]. At the brain level, an association was found between smaller hippocampal volumes and early onset of alcohol dependence in adolescence, possibly accounting for the memory deficits noted above [15]. Moreover, functional neuroimaging studies have detected abnormal brain activations in adolescents with an alcohol use disorder, relative to healthy volunteers, when they were tested during spatial working memory tasks even though task performance did not differ [16, 17]. These findings suggest that the combination of neuroimaging with cognitive measures might be needed to capture the subtle developmental effects of adolescent onset alcohol misuse, which might translate to future addiction.

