## Methods

### Objectives and hypotheses

In 2011, the Co-Venture Trial was funded by the Canadian Institutes of Health Research (CIHR) to test the 4-year impact of the Preventure programme on delaying early onset drinking and binge drinking in students as well as long-term addiction outcomes. A subsequent CIHR grant was awarded for the Neuroventure study, allowing us to add longitudinal neuroimaging measures to test the following objectives/hypotheses:Compare high-risk (IMP and SS) and low-risk youth on measures of brain structure and function to quantify neurocognitive endophenotypes of these two risk profiles prior to exposure to alcohol in adolescence. We expect to observe impaired fronto-striatal connectivity and function during response inhibition in IMP as well as altered function of frontal and sub-cortical regions (i.e., basal ganglia and ventral striatum) during reward anticipation in SS.Measure the correlates of adolescent drinking and binge drinking on the development of brain structure and function in adolescence, controlling for baseline differences in personality, cognitive profiles, and neural measures that are implicated in the predisposition to early onset alcohol misuse. By comparing youth who take up drinking to those who do not (regardless of intervention status), we will test the extent to which binge drinking trajectories are associated with delayed or altered development of fronto-striatal and fronto-limbic networks that mediate response inhibition and anticipation of reward/punishment. Three hypotheses will be examined. i) Global effects: abnormalities will be observed systematically across all measures of brain function and structure, ii) Developmental specificity: alcohol-induced abnormalities will be specific to regions and cognitive processes that are maturing in adolescence, and iii) Interaction effect: alcohol will exacerbate the abnormalities shown to characterize each high-risk group at baseline.Test causal hypotheses by testing whether delaying drinking (through the Preventure Programme) can produce observable protective effects on structural and functional brain development. By comparing high-risk youth who received intervention to those who did not, we will estimate an intervention effect on structural and functional brain outcomes, which again might be expressed globally across the brain, or more specifically in those areas developing during adolescence or most abnormal in high-risk groups (as revealed in objective 1).

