#### Statistical analyses

The main objectives of the statistical analyses will be to characterize differences for fMRI, cortical thickness, VBM, DWI and behavioral measures between high (SS and IMP) and low-risk youth, binge drinkers and non-drinker trajectory, and those assigned to the intervention or not (with and without exposure to alcohol) over time. Two- and three-way repeated measures analyses of covariance (ANCOVA) will be performed based on region of interest (ROI) scores with covariates such as age, socioeconomic status, pubertal stage, IQ, and other drug use. For cortical thickness and VBM only a-priori defined ROI will be used (i.e., prefrontal lobes, basal ganglia, limbic brain regions and corpus callosum), as previous studies have shown that alcohol affects these regions. For fMRI, we will conduct both exploratory and ROI analyses, and for the DWI data, the regions showing linear age trends in the fMRI analysis will be used as start/finish points for probabilistic tractography.

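### The structural ROI list has no early-maturing comparison region and no whole-brain measure, so cortical thickness and VBM cannot positively show either a global or a maturation-specific effect

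*Protocol article*

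**What the plan says.** Objective 2 (Methods, Objectives and hypotheses) lists three hypotheses about drinking and brain development. The first is "Global effects: abnormalities will be observed systematically across all measures of brain function and structure". The second is that "alcohol-induced abnormalities will be specific to regions and cognitive processes that are maturing in adolescence". The third, an interaction with baseline risk profile, is not at issue here. Objective 3 carries the same choice over to the intervention effect, "which again might be expressed globally across the brain, or more specifically in those areas developing during adolescence", and adds a further option: the areas most abnormal in the high-risk groups.

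The Statistical analyses section then fixes the structural analysis: "For cortical thickness and VBM only a-priori defined ROI will be used (i.e., prefrontal lobes, basal ganglia, limbic brain regions and corpus callosum". The reason given is "as previous studies have shown that alcohol affects these regions". For fMRI the same paragraph plans exploratory as well as ROI analyses. For diffusion imaging it seeds tractography from regions that show linear age trends in the fMRI data.

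The Background supplies the maturation account: "brain maturation in both grey and white matter follows a postero-anterior trajectory across the cortex", with frontal areas and the tracts arising there maturing later. The reward system (striatum, medial and orbital prefrontal cortex) is said to have a course that "follows a non-linear maturation that eventually caps by mid-adolescence". The Data analysis section describes cortical thickness at 81,924 vertices and segmentation of the T1 image into grey matter, white matter and cerebrospinal fluid.

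**The concern.** Separating a global effect from a maturation-specific one needs measurements where the two predictions differ, that is, in tissue that is not maturing in adolescence. The structural analysis is closed to four region families chosen for sensitivity to alcohol. None is designated as a comparator, and no whole-brain structural analysis or summary is listed.

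The Abstract asks whether early alcohol use produces global atrophy or disturbs particular maturing systems. Atrophy is a structural claim, so the structural data are the natural evidence on it. As planned, the most likely positive result, effects across the listed ROIs, would leave that part of the question open.

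This is a stated exclusion and not a detail left to another document. The word *only*, followed by a closed list, rules other regions out, and the contrast with the fMRI sentence shows that structure is deliberately handled differently.

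**Working it through.** No figure in the protocol bears on this point, so there is nothing to reproduce. The check compares what each hypothesis predicts with what is measured.

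**Step 1: predictions by region type**

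| Region type | Global effect predicts | Maturation-specific effect predicts | In the thickness/VBM plan? |
|---|---|---|---|
| Maturing in adolescence (on the Background's account: frontal cortex, striatum and medial/orbital prefrontal cortex) | Abnormal | Abnormal | Yes |
| Early-maturing (posterior cortex, on the stated gradient) | Abnormal | Not abnormal | No |
| Whole-brain measure | Abnormal | Depends on the share of maturing tissue | No |

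Only the second row separates the hypotheses cleanly, and it is absent. The Background gives no maturation timing for limbic regions or for the corpus callosum as a whole, so the protocol offers no basis for using either as a comparator.

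**Step 2: reading the possible results in the four families**

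- All affected: fits both hypotheses.
- One family clearly and precisely unaffected: counts against a strictly global effect. It does not show specificity unless that family is known not to be maturing, and the protocol does not say so of any.
- None affected: supports neither.

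No pattern positively establishes either hypothesis.

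**Step 3: do other parts of the plan fill the gap for structure?**

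- Thickness is defined as the distance between the white and grey surfaces. It therefore does not apply to the basal ganglia or corpus callosum, which leaves prefrontal and limbic cortex for that measure.
- Diffusion tractography starts and ends in regions with age trends, so it is itself selected on maturation.
- Exploratory fMRI and the cognitive tasks bear on function, not on tissue.

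**Step 4: are the data there?** Yes. The Data analysis section yields thickness over the whole cortical surface and segmented tissue, so the restriction lies in the analysis and not in the acquisition.

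**Step 5: what an added comparison region could detect (illustration)**

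From the documents: 60 high-risk participants with and 60 without the intervention, and 15% attrition, so 60 × 0.85 = 51 per group. Assumed: a standardised group difference d = 0.5 in the target region and 0 in the comparison region, between-region correlation ρ, two-sided α = 0.05.

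The group contrast on the target-minus-comparison difference has standardised size d / √(2(1 − ρ)) and noncentrality equal to that size × √(51/2), with 100 degrees of freedom.

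| ρ | Standardised size | Noncentrality | Power |
|---|---|---|---|
| 0.3 | 0.5/√1.4 = 0.423 | 0.423 × 5.050 = 2.13 | 0.56 |
| 0.5 | 0.5/√1.0 = 0.500 | 0.500 × 5.050 = 2.52 | 0.71 |
| 0.7 | 0.5/√0.6 = 0.645 | 0.645 × 5.050 = 3.26 | 0.90 |

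The even split matches the intervention comparison of Objective 3. For Objective 2 the split is between drinkers and non-drinkers. The Discussion expects about 95% of high SS and IMP youth to report binge drinking at 15. Applied to all 120 high-risk participants, that is 120 × 0.95 = 114 against 6. The intervention should lower the proportion, and the rate among the 30 low-risk participants is not given, so the real split is unknown. A strongly uneven one would reduce power below the table.

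**The case against.** Restricting structural tests to a-priori regions is a recognised way to control multiplicity in a sample of 150, and it invalidates no planned estimate. Risk-group, drinking and intervention effects within the listed ROIs remain testable, as does the interaction hypothesis. That stands, and it is why the remedy keeps the four families.

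A reader might infer that the study as a whole cannot separate global from specific effects. The documents do not support this. The hypotheses cover function and cognitive processes as well as structure. fMRI keeps an exploratory analysis, and the Behavioral assessment section provides tests of inhibition, working memory, memory recall, risk taking and IQ.

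A reader might also infer that the structural data say nothing about the choice, or that the global hypothesis cannot be refuted. This too goes beyond the text. A hypothesis that "abnormalities will be observed systematically across all measures of brain function and structure" is contradicted by a precise null in any listed ROI. The families were chosen for alcohol sensitivity and not for a common maturation schedule, so differing patterns among them could carry some information.

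Finally, no sentence in the protocol says that a positive ROI result will be reported as specific. That misreading is possible but not planned.

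What remains is that an effect across all the ROIs would be ambiguous, and that the structural plan contains no measure able to resolve it.

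**Conclusion.** The concern holds for cortical thickness and VBM. The protocol poses a global-versus-specific question that includes structure, then closes the structural analysis to regions where an effect across the board fits both answers. Neither answer can be positively shown; evidence against a strictly global effect is possible through a precise null in one family.

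The size is one of interpretation: none of the four listed families is designated as a comparator, and no whole-brain structural measure is listed. No planned effect estimate is biased by this. The conclusion rests on the protocol's own maturation gradient and on reading the ROI list as closed, which its wording requires.

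**What to change.** In Statistical analyses, keep the four target families and add prespecified early-maturing comparison ROIs, for example posterior or primary sensorimotor cortex in line with the Background's gradient, taken from the maps already produced.

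- Test specificity by a region-class (target versus comparison) × group × time interaction, reported with its confidence interval.
- Claim a specific effect only if that interaction is shown.
- Claim a global effect only if an effect is shown in the comparison regions themselves. If similarity between region classes is asserted, the interval should also lie within a prespecified margin. A non-significant interaction alone is not evidence of a global effect.
- Mean cortical thickness and total grey-matter volume contain the target regions, so report them as descriptive summaries or compute them with the target ROIs excluded.

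Alternatively, leave the ROI list as it is and state that the global-versus-specific claim will be confined to fMRI and cognition.

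The cost is a change of analysis wording with no new scan or participant. The downsides are a few more tests in the multiplicity count and possibly modest power for the interaction, especially if drinker and non-drinker groups are unequal.

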## Discussion

Imaging studies using different modalities have consistently reported that alcohol use during adolescence is associated with abnormalities in brain structure, function and connectivity [72]. However, the critical question of whether these anomalies are consequences of alcohol abuse or preexisting vulnerability factors for early use and misuse remains unanswered in the literature. This prospective, intervention study will allow us to identify brain, cognitive, and behavioral factors that precede (and predispose to) adolescent alcohol misuse versus factors that are consequential to such use. Moreover, this unique study will enable us to test whether an early alcohol prevention intervention produces protective effects on brain structure, function and connectivity in adolescents, while controlling for potential pre-morbid factors associated with a susceptibility to early onset drinking. By focusing on the neural correlates of adolescents at risk for harmful drinking, and by examining the effects of adolescent drinking and binge drinking on the development of brain structure and function, the study will extend the knowledge gained from other large-scale studies (e.g., European Commission FP6-Health www.imagen-europe.com and National Institutes of Health’s “Longitudinal Studies on the Impact of Adolescent Drinking on the Adolescent Brain”). Perhaps more importantly, this innovative experimental design will allow us to test the causal relationship between early alcohol exposure and neurocognitive and addiction outcomes by showing that delaying drinking in those most at-risk protects normal neurocognitive development.

The main strengths of the study are that (i) the selection, intervention and measurement models are highly time-sensitive, capturing critical periods (12–14 and 14–16 years of age) when personality endophenotypes translate to risk for binge drinking and when early intervention can produce preventative effects. Furthermore, (ii) this critical period appears to overlap with the age at which drinking onset is highly related to future drinking [73], and when important brain maturation occurs [10]. In addition, (iii) this research design is highly powered as our screening procedure, which is largely based on personality assessment at 12–13 years of age, identifies individuals, SS and IMP youth, for whom binge drinking is almost certain to develop within the next 12 months. Our previous research has shown that at 13 years of age, high SS and IMP adolescents have normal rates of drinking and binge drinking (around 40%), but experience a rapid rate of onset of binge drinking between 14 and 15 years of age, with approximately 95% reporting binge drinking at 15 years of age [34]. We will also be able to (iv) test critical questions on the causal pathway from premorbid risk markers to early onset drinking, disruptions in brain function and, in turn, addiction outcomes. Finally, by being embedded into a larger population-based 5-year longitudinal randomized controlled trial, we will be able to directly (v) test the generalizability of our sample and findings to the general population, which is unique for pediatric neuroimaging studies, which tend to involve highly selective clinical samples or families with high education and socio-economic characteristics.

Harmful alcohol use in early adolescence is associated with a more severe and protracted course of adult alcohol abuse and dependence and greater risk for severe psychiatric and other consequences of drinking. While these facts clearly indicate a need to focus our efforts on early intervention and prevention, particularly with vulnerable groups, only a fraction of the annual health budget dedicated to the treatment of substance abuse goes toward alcohol and drug prevention. This research will directly feed public knowledge on the harms associated with youth alcohol misuse, as well as the evidence base for selective interventions. The expected results will show direct effects of drinking on brain development and the benefits of early intervention and prevention efforts, effects that will be difficult to ignore in public policy on youth drinking.

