**Methods:**

A subsample of 120 youth at high risk for substance misuse and 30 low-risk youth will be recruited from the Co-Venture trial (Montreal, Canada) to take part in this 5-year follow-up neuroimaging study. The Co-Venture trial is a community-based cluster-randomised trial evaluating the effectiveness of school-based personality-targeted interventions on substance use and cognitive outcomes involving approximately 3800 Grade 7 youths. Half of the 120 high-risk participants will have received the preventative intervention program. Cognitive tasks and structural and functional neuroimaging scans will be conducted at baseline, and at 24- and 48-month follow-up. Two functional paradigms will be used: the Stop-Signal Task to measure motor inhibitory control and a modified version of the Monetary Incentive Delay Task to evaluate reward processing.

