### The Preventure Programme

The Preventure Programme is a school-based alcohol prevention programme targeting four specific personality risk factors for adolescent alcohol misuse: impulsivity, sensation seeking, hopelessness and anxiety sensitivity [34, 35]. The Substance Use Risk Profile Scale (SURPS) [36] has been developed by our team to enable us to identify high-risk youth based on these personality risk dimensions [29, 37]. The intervention programme, based on a cognitive-behavioral model, involves delivering two 90-min group sessions to adolescents who screen positive on one of these four personality traits in school screening. Five randomized controlled trials with high school students revealed that personality-targeted interventions reduce rates of drinking and binge drinking by up to 50% [34, 38, 39], and these effects have been shown to last up to 3 years [35, 40, 41]. Despite these very promising findings, these outcomes may underestimate the true benefits of early intervention as our previous evaluations did not assess brain function and maturation.

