
### The Co-Venture Trial (from which the participants are recruited)

This study uses a cluster-randomized controlled design in which 31 schools (cluster) agreed to conduct annual surveys for 5 years with all consenting adolescents (*N* = 3826) who were enrolled in Grade 7 in September 2012. Schools were randomly assigned to i) be trained and assisted in the delivery of the Preventure programme to Grade 7 high-risk adolescents or ii) not be exposed to the intervention. Adolescents were screened using the SURPS [36] during their Grade 7 year and invited to participate in personality-specific Preventure workshops if they scored one standard deviation above the school mean on one of the four SURPS dimensions. The Co-Venture clinical Trial is registered on www.ClinicalTrials.gov, “Co-Venture: a Cluster Randomized Trial Investigating the Effects of Selective Intervention on Adolescent Cognitive Development and Addiction”, study NCT01655615.

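### The programme-versus-no-programme contrast estimates the total effect of Preventure; it becomes a causal test of early alcohol exposure only if the programme reaches the brain solely through drinking, which the article neither states nor defends

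*Protocol article*

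**What the plan says.** Objective 3 (Protocol article, Objectives and hypotheses) begins: "Test causal hypotheses by testing whether delaying drinking (through the Preventure Programme) can produce observable protective effects on structural and functional brain development". The comparison given for it is: "By comparing high-risk youth who received intervention to those who did not, we will estimate an intervention effect on structural and functional brain outcomes". The last sentence of the first Discussion paragraph then says that the design will let the authors "test the causal relationship between early alcohol exposure and neurocognitive and addiction outcomes by showing that delaying drinking in those most at-risk protects normal neurocognitive" […].

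On the programme, the section The Preventure Programme names impulsivity and sensation seeking among its four target traits and describes it as "based on a cognitive-behavioral model, involves delivering two 90-min group sessions to adolescents who screen positive on one of these four personality traits". The Abstract says the parent trial evaluates the "effectiveness of school-based personality-targeted interventions on substance use and cognitive outcomes". Schools in the other arm were randomised to "not be exposed to the intervention" (The Co-Venture Trial).

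The Statistical analyses section also compares the assigned groups according to whether there was alcohol exposure, and lists use of other drugs among the possible covariates. The article names no mediation or instrumental-variable analysis.

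**The concern.** Schools were randomised to the programme, not to drinking. An arm difference in a brain measure is therefore the sum of everything the programme does. To attribute it to delayed alcohol use, one must assume that no other route from programme to brain exists.

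The article leads with the question of whether early alcohol use marks or causes later problems, and the arm contrast is its main experimental answer. If the assumption fails, a positive contrast could be reported as evidence that early drinking harms the developing brain when some or all of it came by another route. The opposite error is also possible: a null contrast would not show that alcohol is harmless. The closing Discussion paragraph aims the results at public policy on youth drinking, so the distinction affects what may be claimed.

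**Working it through.** There is no stated figure to reproduce. The check has three parts.

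**1. Do the documents support a single pathway through drinking?**

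- Programme content: cognitive-behavioural, with impulsivity and sensation seeking among its targets (The Preventure Programme).
- Outcomes: the Impulsivity section links impulsivity to orbitofrontal grey matter volume and to frontal activity during failed inhibition. The Sensation seeking section separates the two traits by activation in failed inhibition and in reward anticipation. The two scanner tasks, Stop-Signal and Monetary Incentive Delay, probe these processes.
- Parent trial: cognition is an outcome alongside substance use (Abstract).
- Comparator: no exposure to the programme, and no attention or alternative-content control is described.

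The targeted traits are thus the ones tied to the imaging outcomes. A route that bypasses alcohol is plausible on the article's own account, though not shown.

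**2. What does the arm difference identify?**

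Arm difference = (reduction in binge prevalence) × (effect of avoiding bingeing) + (programme effect not through drinking).

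Inputs: about 95% bingeing at age 15 in high-risk youth (Discussion) and a 40 to 60% reduction (Abstract; The Preventure Programme says up to 50%). Effects in SD units are assumptions.

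- Bingeing gap: 0.95 × 0.40 = 0.38; 0.95 × 0.50 = 0.475; 0.95 × 0.60 = 0.57.
- At a gap of 0.475, an alcohol effect of 0.80 SD with no other route gives 0.475 × 0.80 = 0.38 SD. No alcohol effect and a direct programme effect of 0.38 SD also gives 0.38 SD. The contrast cannot tell these apart.
- If the arm difference were divided by the gap to obtain a drinking effect, an ignored direct effect of 0.10 SD would add 0.10/0.57 = 0.18 SD to 0.10/0.38 = 0.26 SD. The plan makes no such ratio estimate, so this shows only the sensitivity of one that might be added.

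**3. Does splitting by alcohol exposure separate the routes?**

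Drinking after baseline is a post-randomisation variable that the programme is meant to change. Drinkers in the programme arm are then a more liable subset than drinkers in the control arm, where nearly everyone drinks. The few control non-drinkers are unusually low in liability. Neither stratum compares like with like.

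A simulation of 2,000,000 subjects illustrates this. It assumed bingeing of 95% (control) and 47.5% (programme), and a latent trait correlated 0.5 with drinking liability and carrying a −0.5 SD effect on the outcome. Differences are programme minus control.

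| Assumed truth | Overall difference | Among drinkers | Among non-drinkers | Correct direct effect |
|---|---|---|---|---|
| Alcohol −0.80 SD, no direct effect | 0.38 | −0.18 | −0.33 | 0 |
| No alcohol effect, direct effect 0.38 SD | 0.38 | 0.20 | 0.06 | 0.38 |

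In neither case does the split recover the direct effect. The same reasoning applies to adjustment for other drug use if it is measured after baseline. The sizes depend on the assumed trait effects; the loss of the randomised comparison does not.

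**The case against.** The strongest reply is that the text is more careful than this point suggests. Objective 3 speaks of testing, and its second sentence announces an intervention effect, which is already total-effect wording. The article also measures other drug use, plans to consider alcohol exposure, and says in the Discussion that it will test the causal pathway from risk markers through drinking to brain function. The method for that may sit in a full protocol or analysis plan that is not shown.

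Much of this stands, and it rules out several stronger readings that a reader might infer:

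- That Objective 3 treats an arm difference as proof. It does not. The overreach is in its opening sentence and in the Discussion sentence that follows from it.
- That the programme is a treatment of impulsivity or trains self-control. The article says only that it targets personality risk factors.
- That the closing Discussion statement, "The expected results will show direct effects of drinking on brain development", rests on the arm contrast. It may instead rest on Objective 2, the observational comparison of drinkers with non-drinkers regardless of arm. The documents do not settle which.
- That the trial would report an alcohol effect inflated by a known factor. The plan is repeated-measures ANCOVA on region scores, with no division by the bingeing gap.

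What does not stand is the rescue by other analyses. The exposure split and the drug-use covariate can both be altered by the programme. An unseen mediation analysis would need no unmeasured mediator-outcome confounding, and an instrumental-variable analysis would need no direct effect. The point concerns what the article asserts from the contrast, not the absence of a method section.

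**Conclusion.** The point holds as one of interpretation. The randomised contrast supports a conclusion about the programme's total effect on brain outcomes. It does not by itself support the Discussion's conclusion about early alcohol exposure, because the required assumption of no other pathway is unstated and the article's own background makes it doubtful.

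No sample size, estimate or procedure is shown to be wrong. The size of any misattribution is unknown: it runs from none, if all of the effect passes through drinking, to the whole arm difference, if none does. The numerical illustrations rest on assumed SD effects and on bingeing figures that the article takes from earlier studies.

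**What to change.** 1. Reword the opening of Objective 3 and the last sentence of the first Discussion paragraph so that the arm contrast, not conditioned on alcohol or drug use after baseline, is concluded as the total effect of the programme. Add that a null contrast will not be read as absence of harm from alcohol.
2. Report arm effects on other drug use, and on the SURPS traits where they are remeasured, as competing pathways.
3. Claim an effect through delayed drinking only from a secondary mediation or instrumental-variable analysis labelled with its assumptions (no unmeasured mediator-outcome confounding, or no direct effect), with a sensitivity range for a direct programme effect.
4. In the closing Discussion paragraph, do not let the arm contrast support the claim of direct effects of drinking. If that claim rests on Objective 2, say so and describe the evidence as observational.

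A timing check, showing that brain differences do not precede divergence in drinking, is not available. Scans take place only at baseline, 24 and 48 months, and the annual surveys collect no brain measures.

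The cost is a few sentences and one secondary analysis, using trait data only where SURPS is remeasured. The downside is a weaker headline claim.
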